### Measures

The outcome measures used are reliable and valid with cancer survivors. We selected short form versions, where available, to reduce participant burden. All outcome measures are assessed at 3 time points: baseline (immediately prior to intervention), 2 weeks after the last session, and 3 months after the last session. All outcome measures and assessment instruments are listed in Table 2.

**Table 2 Tab2:** Schedule of enrollment, interventions, and assessments

	Enrollment eligibility T0	Allocation baseline T1	Post-allocation			
			Sessions 1–4	Sessions 1–5	T2 2 weeks	T3 3 months
ENROLLMENT						
Eligibility screen	X					
Informed consent	X					
Allocation		X				
INTERVENTIONS						
OC intervention				X		
SS intervention			X			
ASSESSMENTS						
Primary outcomes						
Reproductive distress Fertility Problem Inventory (FPI)-Relationship Concern Domain		X			X	X
Sexual distress Sexual and Relationship Distress Scale (SaRDS)		X			X	X
Secondary outcomes						
Relationship functioning Dyadic Adjustment Scale (DAS-7)		X			X	X
Relationship intimacy Miller Social Intimacy Scale (MSIS)		X			X	X
Communication about reproductive concerns Couples’ Illness Communication Scale (CSIS)		X			X	X
Communication about sexual concerns Couples’ Illness Communication Scale (CSIS)		X			X	X
Sexual function (female) Female Sexual Function Index (FSFI)		X			X	X
Sexual function (male) International Index of Erectile Function (IIEF)		X			X	X
Sexual satisfaction General Measure of Sexual Satisfaction (GMSEX)		X			X	X
Depressive symptoms Patient Health Questionnaire Depression Scale (PHQ-8)		X			X	X
Health-related quality of life PROMIS Global 10 v1.2		X			X	X
Self-efficacy^a^ Self-Efficacy to Communicate about Sex and Intimacy (SECSI)		X			X	X
Mediating variables						
Dyadic coping	Dyadic Coping Inventory (DCI)	X			X	X
Communication quality	Communication Patterns Questionnaire- Short Form (CPQ-SF)	X			X	X

^a^Cancer survivor-only measure

Intervention acceptability and appropriateness and interventionist assessments are measured 2 weeks after the last session. Two process measures (perceived usefulness and session-specific evaluations) are measured during the intervention.

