Multilevel modeling (MLM; SPSS Version 27) with REML will be used to test Aim 1a for both the primary (reproductive and sexual distress) and secondary outcomes (relationship outcomes and psychosocial health outcomes). These models will examine mean differences in outcomes between OC and SS over time (baseline, 2 weeks, 3 months) and across role (i.e., survivor versus partner) for outcomes measured from both partners. In our primary analyses, time, treatment, and role will be treated as categorical, and models will include all main effects and interactions among these variables. Evidence of treatment efficacy will be assessed by the interaction between time and treatment as we expect no treatment differences at baseline, but we expect to see such differences after the intervention. These models will include random intercepts for survivors and partners, as well as the correlation between the intercepts (i.e., if a survivor is high in average distress across time, is the partner high as well?). They will also include a time-specific correlation between the partners’ residuals (i.e., if a survivor is especially distressed at a particular time point, is the partner especially distressed at that time as well?). In addition to being able to model the interdependence between survivors and partners, the MLM approach has the advantage that it does not delete participants with missing data at some time points and so this analysis utilizes all available data. Outcomes measured only for survivors or only for partners will also be analyzed using MLM, but in this case role will not be included as a predictor and the random effects will include only a random intercept and residual variance.

Covariates to be assessed include age, time since diagnosis, cancer stage, metastatic status, number of children, relationship duration, income, race, ethnicity, and sexual orientation. To determine which covariates should be included in the analyses, preliminary analyses will be conducted in which each outcome is predicted by the full set of qualifying covariates. Only those covariates that predict at least one outcome significantly will be included in the analyses. Once the set of covariates are determined in this way, the same set of covariates will be included in all analyses.

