Exploratory Aim 1b posits a mediational model in which the effects of the intervention on both partners’ primary outcomes are mediated by both partners’ dyadic coping and communication. To examine mediation, the statistical package MPLUS will be used to estimate and test the indirect effects of the treatment on 3-month outcomes via the patient’s and partner’s dyadic coping and communication measured 2 weeks after the intervention. The same set of covariates used in tests of Aim 1a will be included.

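### The Aim 1b mediation model is specified without baseline coping, communication or distress, so its mediator-to-outcome path is confounded and can yield a false indirect effect if OC shifts the mediators

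*Protocol article*

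**What the plan says.** For Aim 1b, the Statistical plan section of the Protocol article will "estimate and test the indirect effects of the treatment on 3-month outcomes". The route is each partner's "dyadic coping and communication measured 2 weeks after the intervention". On adjustment it states: "The same set of covariates used in tests of Aim 1a will be included".

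The Aim 1a set is defined just before, in the same section: "Covariates to be assessed include age, time since diagnosis, cancer stage, metastatic status, number of children, relationship duration, income, race, ethnicity, and sexual orientation". It is then narrowed: "Only those covariates that predict at least one outcome significantly will be included in the analyses". After that step, "the same set of covariates will be included in all analyses". So the set can only shrink from ten candidates, none of which is a baseline mediator or a baseline distress score.

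The baseline scores exist. The Measures section says "All outcome measures are assessed at 3 time points", and Table 2 marks both mediator instruments (DCI and CPQ-SF) at T1, T2 and T3.

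**The concern.** Randomisation makes the treatment-to-mediator path (a) a fair comparison. It does nothing for the mediator-to-outcome path (b), because nobody is randomised to a level of coping. If couples who cope and communicate well are also persistently less distressed, coping at T2 will predict distress at T3 even when coping has no effect on distress. Measuring the mediator before the outcome does not remove this. The baseline scores are the collected variables best placed to reduce it.

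Aim 1a has its own protection: baseline distress is one of the repeated time points, and stable differences go into the random intercepts. Aim 1b carries over the covariates, and its text describes no random intercept, change score or baseline adjustment.

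What is at stake is the claim about mechanism. The Discussion presents the mediation analyses as novel and expects them to inform later work on the intervention.

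**Working it through.** The plan gives no figure for the mediation analysis, so there is none to reproduce. The check asks what the stated specification does when the mediator has no effect on distress.

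**Inputs from the Protocol article**
- 100 couples and 20% attrition (Sample size section): 100 × (1 − 0.20) = 80 couples at T3.
- 1:1 allocation (Randomization section): 40 per arm.
- Mediator at T2, outcome at T3, no T1 scores in the covariate list (Statistical plan).

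**Assumed inputs, not in the documents**
- Retest correlation r of each measure: .6 to .8.
- Correlation c between the stable parts of mediator and distress: −.4 to −.6.
- Shift a of the mediator by OC relative to SS: 0, 0.2, 0.3 or 0.5 SD.
- True effect of mediator on distress: 0.
- One person per couple and one mediator, a simplification of the dyadic model.

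**Model.** Within arm, each score has unit variance and is √r × trait + √(1 − r) × noise. The mediator and distress traits correlate at c, and a is added to the T2 mediator in the OC arm.

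**Step 1: the false b path by algebra.** Without T1 scores, b = r × c.
- Smallest: .6 × (−.4) = −0.24.
- Largest: .8 × (−.6) = −0.48.

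The true value is 0. With the T1 mediator alone, b = r × c / (1 + r), which runs from −0.24 / 1.6 = −0.15 to −0.48 / 1.8 = −0.27. With T1 mediator and T1 outcome, simulation gives about −0.04 to −0.11.

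**Step 2: the false indirect effect, a × b, without T1 scores.**
- a = 0.5: −0.12 to −0.24 SD.
- a = 0.3: −0.07 to −0.14 SD.
- a = 0.2: −0.05 to −0.10 SD.
- a = 0: centred on 0, whatever b is.

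**Step 3: how often mediation is falsely declared** (simulation, n = 80; ranges run over r and c).

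| Shift a | No T1 scores | T1 mediator and T1 outcome added |
|---|---|---|
| 0.5 SD | about 35-61% | about 6-11% |
| 0.3 SD | about 16-27% | about 4-7% |
| 0.2 SD | about 9-14% | about 2-3% |
| 0 | 2-6% | under 1% |

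Repeating the simulation, with both paths required to be significant at 5%, agreed to within about two percentage points.

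**Step 4: the ceiling.** If both paths must be significant, the unadjusted rate cannot exceed the power for path a. At 40 per arm that power is about 60% for 0.5 SD, 26% for 0.3 and 14% for 0.2. The top of each unadjusted range sits at this ceiling, within simulation error: under the stronger assumptions, almost every trial that detects a shift in the mediator also declares mediation.

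**The case against.** **The text does not say that nothing else enters.** It says the Aim 1a set will be included. A reader might infer that the model is limited to those covariates, and the document does not support that: a fuller analysis plan could add baseline scores as part of the path model. This stands as a limit on the claim. It does not dissolve it, because the article fixes mediator timing, outcome timing and a named covariate set, and followed as written that specification is confounded.

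**The abstract calls the primary outcomes change in distress.** If Aim 1b meant a change from baseline, the T1 outcome would be in the model. Under a perfectly stable trait with equal retest correlation, subtraction would even cancel the confounding. But the Aim 1b text speaks of 3-month outcomes and mentions no change score, and Table 3 lists distress itself at 3 months. If the T1 outcome entered as a covariate without the T1 mediator, false mediation would still be about 9-27% at a 0.5 SD shift and 5-11% at 0.3 SD (retest .6 to .7). The T1 mediator is absent on either reading.

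**The size depends on the shift.** SS is an active comparator that teaches the same coping and communication skills, and the Discussion expects benefit in both arms. The documents give no between-arm effect on the mediators, and the effects in the sample size section run from d = .27 to .36. A shift of 0.5 SD may therefore be generous. This stands, so the full range is shown. A reader might infer that any shift at all will look like mediation. That is too strong: at 0.3 SD, 73-84% of simulated trials declare none.

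**The remedy is partial and the aim is exploratory.** Both are true. The simulation covers one person and one mediator, so it does not test the full dyadic model.

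**Conclusion.** The concern holds in a conditional form. As published, Aim 1b relates T2 mediators to T3 outcomes with a covariate set that names no baseline mediator or outcome score, and this confounds the path that randomisation leaves open. The confounding turns into a false indirect effect when OC moves coping or communication relative to SS, which is the situation Aim 1b is meant to examine. The false b path of −0.24 to −0.48 and the rates in the table rest on assumed retest and trait correlations and on a single-person model; the direction does not depend on their exact values, the size does. A reader might go further and doubt the efficacy result. The documents do not support that, because Aim 1a treats baseline distress as a repeated time point and no efficacy conclusion depends on the mediation model.

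**What to change.** In the Aim 1b MPLUS model, add each partner's T1 mediator scores and T1 outcome score as predictors of the T2 mediators and the T3 outcomes, and say so alongside the covariate sentence. Report the indirect effects as exploratory and not as causal proof of mechanism, since residual confounding remains: the T1 scores are imperfect measures of the stable differences.

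No new data or visits are needed. The cost is parameters at 80 to 100 dyads. With one outcome, one mediator and both partners, there are 4 T1 scores and 4 equations, so up to 4 × 4 = 16 added paths. With two mediator scores fitted jointly it is up to 6 × 6 = 36. Fitting one mediator at a time keeps the model smaller.

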#### Sample size estimate/ power calculations

A sensitivity power analysis was conducted using the program G*Power and anticipating an initial sample of 100 couples (*N* = 200 individuals), and an attrition rate of 20% at the final assessment. Given that the design has two levels of the treatment and three assessments, for outcomes that are assessed on only survivors (or only partners), the study has 90% power to detect small to moderate effects (i.e., *d* = .32) if there is no attrition. With the expected 20% attrition, the study has 80% power to detect effects greater than *d* = .36. Because both partners will complete most of the same outcomes, for these outcomes the effective sample size is larger than the number of dyads but smaller than the number of individuals. Specifically, assuming a cross-dyad correlation of *r* = .4 (e.g., the correlation between the two partners’ distress), the effective sample size to test the treatment by time interaction is 142 without attrition and 114 with attrition. Thus, for these outcomes, without attrition the study will have 90% power to detect effects of *d* > .27 and with attrition it will have 90% power to detect effects of *d* > .30.

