#### Randomization

The study uses 1:1 blocked randomization (groups of 4), stratified by cancer type (breast versus gynecologic) and sexual orientation reported by the cancer survivor (heterosexual versus other). The study statistician generates the randomization sequence, and assignment to condition occurs via REDCap after the dyad has completed both the baseline assessment and videoconference orientation call with study staff. Couples are notified of their intervention assignment after scheduling their first session with the study interventionist. At that time, they receive both a mailed version and link to an electronic version of the participant materials. As with most behavioral interventions, the study interventionist, intervention supervisor, and participants are not masked to condition. However, although participants know whether they are receiving OC or SS, they are not told which of these is the experimental condition. The condition is masked to the PI, biostatistician, and research assistants who will evaluate quantitative outcome data. Quantitative outcome data is also collected via REDCap to minimize contact with participants while collecting study data. Should a review of adverse events reveal significant between-group differences that could warrant unmasking of the study conditions by the study biostatistician.

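### The 80% power attached to d > .36 under 20% attrition does not fit the paragraph's other figures: with 80 couples that effect has about 90% power (minor correction)

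*Protocol article*

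**What the plan says.** All the figures stand in one paragraph of the protocol article, *Sample size estimate/ power calculations*. It introduces a single analysis: "A sensitivity power analysis was conducted using the program G*Power", "anticipating an initial sample of 100 couples" and "an attrition rate of 20% at the final assessment". The design is described once: "the design has two levels of the treatment and three assessments". Four power statements follow.

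- One role only, no attrition: 90% power, d = .32.
- One role only, attrition: "With the expected 20% attrition, the study has 80% power to detect effects greater than" d = .36.
- Both partners, no attrition, effective sample size 142: 90% power, d > .27.
- Both partners, attrition, effective sample size 114: "with attrition it will have 90% power to detect effects of" d > .30.

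The paragraph gives neither the significance level nor the within-person correlation. The *Statistical plan* section names the test of interest: "Evidence of treatment efficacy will be assessed by the interaction between time and treatment".

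**The concern.** Only the second statement carries 80%. Its effect size, .36, is what one obtains by carrying the first statement down to 80 couples at an unchanged 90%. If the power had really been lowered to 80%, the detectable effect should have come out smaller than .36.

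As printed, the step from no attrition to 20% attrition seems to worsen both the detectable effect and the power. In a sensitivity analysis with the power fixed, only the detectable effect changes. This is also the only statement of power for single-role outcomes under the attrition that the trial expects. A reader who sets it beside the both-partner figures would conclude that single-role outcomes are less well covered than they are.

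**Working it through.** **Inputs.** The sample is 100 couples, and 20% attrition leaves 80. There are two arms, three assessments and 1:1 allocation (section *Randomization*). The effective sample sizes of 142 and 114 are as printed. They agree with 200/1.4 = 142.9 and 160/1.4 = 114.3, using the stated cross-partner correlation of .4.

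**Step 1: check without any unstated input.** For one design, with the significance level and the within-person correlation held fixed, power depends essentially on d × sqrt(N).

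| Statement | d | N | d × sqrt(N) | Stated power |
|---|---|---|---|---|
| One role, no attrition | .32 | 100 | 3.20 | 90% |
| One role, attrition | .36 | 80 | 3.22 | 80% |
| Both partners, no attrition | .27 | 142 | 3.22 | 90% |
| Both partners, attrition | .30 | 114 | 3.20 | 90% |

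The products are equal to within rounding, so the four powers must be nearly equal too. Scaling the first statement at 90% power:

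- N = 80: .32 × sqrt(100/80) = .358, printed as .36
- N = 142: .32 × sqrt(100/142) = .269, printed as .27
- N = 114: .32 × sqrt(100/114) = .300, printed as .30

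**Step 2: noncentral F.** I used the repeated-measures test of the group-by-time interaction, with f = d/2, noncentrality λ = f² × N × 3/(1 − ρ), and degrees of freedom 2 and 2(N − 2). Alpha = .05 is my assumption. The correlation ρ was set to reproduce the paragraph's first statement (d = .32, N = 100, 90% power), which gives ρ = .402.

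| d | N | λ | Computed power | Stated power |
|---|---|---|---|---|
| .32 | 100 | .16² × 300/.598 = 12.84 | .900 (calibrated) | 90% |
| .27 | 142 | .135² × 426/.598 = 12.98 | .905 | 90% |
| .30 | 114 | .15² × 342/.598 = 12.87 | .901 | 90% |
| .36 | 80 | .18² × 240/.598 = 13.00 | .903 | 80% |

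The two both-partner statements reproduce. The single-role statement with attrition misses by 10 points. With N = 80, the effect detectable at 90% power is .358 and at 80% power .313.

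**Step 3: can another setting rescue the printed pair?**

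- *Implied correlation.* The three 90% statements imply ρ = .402, .393 and .400. Reading d = .36 as 90% gives ρ = .397, in line with them. Reading it as 80% gives ρ = .208.
- *Rounding.* With the true .32 anywhere in .315–.325 and the true .36 anywhere in .355–.365, power at N = 80 stays between .884 and .919.
- *Significance level and sphericity.* Alpha from .01 to .10, or a sphericity correction from .5 to 1, each recalibrated to the first statement, gives .902 to .903.
- *Attrition.* At d = .36, about 61 couples would already give 80% power, which means 39% attrition rather than 20%.

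**The case against.** Four points can be made for the text as it stands.

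1. *The sentence is literally true as a lower bound.* A trial with 90% power at d = .36 also has at least 80%. That holds, but the paragraph reports a sensitivity analysis, and the neighbouring sentences use the same form of words for exact thresholds. Read the same way, this one does not fit.
2. *The authors may have switched to 80% on purpose.* Quoting different powers for different scenarios is legitimate, provided that each pair is right. A switch to 80% would have produced about .31.
3. *The error is conservative.* This stands. Nobody is led to think the trial is better powered than it is.
4. *The outcomes concerned are few and secondary.* This also stands. Table 2 marks one measure, self-efficacy to communicate about sex and intimacy, as survivor-only. The sex-specific function scales may in practice fall mostly in one role, and they are secondary as well.

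A reader might infer that the trial's main power claim is wrong, or that 100 couples is the wrong number. The documents do not support that. Reproductive and sexual distress are measured in both partners and rest on the figures for 142 and 114, which reproduce. The 100 couples are an input to the sensitivity analysis, so they were not derived from this sentence. A reader might also infer that the paragraph proves which number was misprinted. It does not: the pattern favours 80% as a slip for 90%, but only the G*Power output can settle it.

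**Conclusion.** The statement is wrong as written, and the correction is minor. With 80 couples, d = .36 carries about 90% power rather than 80%. Equivalently, the effect detectable with 80% power is about .31 (.308 to .318 over the rounding of .32) rather than .36.

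That the four statements cannot all stand together follows from the printed numbers alone and needs no assumption about alpha or the correlation. The value .31 does rest on assumptions: alpha .05, the interaction test described above, and a correlation calibrated to the paragraph's first statement. The discrepancy understates power for single-role secondary outcomes. It leaves the primary outcomes, the sample size and the planned analysis untouched.

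**What to change.** Look up the G*Power output for N = 80 and restate the one sentence. The likely correction is 90% power to detect effects greater than d = .36, which agrees with the other three statements. If 80% was intended, the effect size should read d = .31. The cost is one sentence, with no change to design, conduct or analysis.

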Key inclusion and exclusion criteria	Ages eligible for study: ≥18 years to 44 years (cancer survivor, partner 1) and ≥18 years (partner 2) Sexes eligible for study: all Accepts healthy volunteers: no
	Inclusion criteria (partner 1): cancer diagnosis between the ages of 18 and 39; current age 18–44; cancer diagnosis between 6 months and 5 years prior to enrollment date; diagnosed with breast or gynecologic cancer; self-reported cancer stages 1–4 at time of diagnosis; committed partner who is willing to participate Inclusion criteria (partner 2): age 18 or older
	Exclusion criteria: survivors and partners are excluded if either partner does not meet the eligibility criteria; both partners must enroll in order to participate.
Study type	Interventional
	Allocation: randomized intervention. Parallel assignment masking: double blind (investigator, outcomes assessor)
	Primary purpose: supportive care
	Phase III
Date of first enrolment	September 2021
Target sample size	100 dyads (200 individuals)
Recruitment status	Recruiting
Primary outcome(s)	Reproductive distress, Sexual distress (time frame: 3 months)
Key secondary outcomes	Communication about reproductive concerns, communication about sexual concerns, depressive symptoms, sexual function, relationship quality, relationship intimacy, sexual satisfaction, self-efficacy to communicate about sex and intimacy, and quality of life

